### **10.2. Follow-up Assessment**

Patient follow-up care will be at the discretion of the investigator at the local site. It is suggested that follow-up care be in accordance with the Cancer Care Ontario guidelines. For the purposes of collection of study related data, patients will be followed for approximately 5 years. Assessments will be calculated from the date of randomization.

Patients will be assessed every 6 months ( $\pm 14$  days) for the first 2 years (Year 1 and 2). At each follow-up visit, patients will be required to return to the clinic to assess current disease status. ECOG performance status will also be assessed and documented. The two QoL questionnaires (EORTC QLQ-30 version 3 and QLQ-CX24) will be completed by the patient at 3, 6, 12, 18 and 24 months after randomization. These questionnaires can be either mailed to the patient or completed by the patient at a clinic visit (see *Appendix IV*).

To perform the health economic evaluation, a limited set of questions on health care resource utilization and patient utility will be incorporated into the data collection. The health utility questionnaire (EQ-5D) will be completed by the patient at 3, 6, 12, 18 and 24 months after randomization. This questionnaire can be either mailed to the patient or completed by the patient at a clinic visit (see *Appendix V*).

Information on a patient's cancer status (free of disease or not) and overall survival will be abstracted from their cancer centre or hospital records, or by contacting the family physician at least once a year for Years 3, 4, and 5.

On completion of the 5 years of follow-up required by this study, further assessment of the patient will be according to the oncologist's or local institutional practice; patients will not be restaged at the end of the 5-year follow-up period.

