All tests will be two-sided and based on an intent-to-treat analysis. A p-value of 0.05 or less will be considered statistically significant. In addition, 95% confidence intervals will be constructed for outcomes of interest. All data analysis will be performed using the latest versions of SAS (Cary, NC) and using StatXact (Boston, MA).

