### **13.3. Analysis Sets**

All patients who are randomized will be included in the Full Analysis set. All patients who complete the baseline QoL and at least one follow-up QoL questionnaire will be included in the QoL Analysis set.

Analysis of the treatment delivered, EFS and OS will be based on the Full Analysis set with patients included in groups according to their randomized allocation (i.e. intention-to-treat principle). A secondary analysis of treatment delivered, EFS and OS will be performed on the protocol evaluable analysis set, defined as the subset of patients in the Full Analysis set excluding patients with disease which has spread to distant organs. Analysis of QoL and economic outcomes will be based on the QoL Analysis set. Investigation of the prognostic ability of PET SUVs will be based on the patients who underwent PET-CT.

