## APPENDIX IX: ECONOMIC ANALYSIS

### Economic Evaluation

#### Costs

We have recently worked with Decision Support Services at Hamilton Health Sciences to successfully obtain costs for treatments, tests, medications, hospitalizations from the Ontario Case Costing Data Base for two of OCOG's other PET trials in lung cancer and breast cancer. We will use the same approach for this trial for costs related to hospitalizations, tests, procedures, medications and the use of other healthcare services. Costs related to physician services will be taken from the recent OHIP payment schedule. For chemotherapy costs we will employ a bottom up costing approach. For radiotherapy costs, we will review funding relationships between individual cancer centres, CCO and the MOHLTC to determine appropriate costs. For example, currently the MOHLTC reimburses cancer centres \$3500 per new patient radiated.

Total healthcare cost including all imaging and treatment will be calculated for each patient and averaged across patients in each study arm. Once patients develop recurrence of their cancer, treatments will vary. We will capture what treatments were received and obtain costs estimates for these but further data collection will not take place.

In addition to the two cancer specific QoL questionnaires, utilities will be estimated using the EQ-5D measurement system. The EQ-5D is a reliable and valid questionnaire designed to estimate societal valuations of the quality of life of patients (utilities). For this analysis, the UK tariff for estimation of utilities will be adopted. The EQ5D will be used to estimate utility values at each assessment point. These will then be aggregated using area under the curve methodology controlling for baseline utility value to allow estimation of quality adjusted life years (QALYs).

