### Time Horizon

Primary analysis will have a time horizon of two years reflective of the period of data capture within the clinical trial. Secondary analysis will involve forecasting costs and utility values up to a time horizon of ten years. Costs and benefits will be discounted at 5%.

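### The economic analysis is restricted to patients with a baseline and a follow-up QoL form, although Appendix IX defines its terms by randomized arm and the primary outcome uses all randomized patients

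*Protocol*

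**What the plan says.** Protocol section 13.3 defines two main sets. For the first, "All patients who are randomized will be included in the Full Analysis set". For the second, "All patients who complete the baseline QoL and at least one follow-up QoL questionnaire will be included in the QoL Analysis set". Treatment delivered, EFS and OS are analysed on the first. For the economic work the rule is "Analysis of QoL and economic outcomes will be based on the QoL Analysis set".

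Other parts of the protocol bear on this:

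- Section 13.1 sets the general principle: "All tests will be two-sided and based on an intent-to-treat analysis". It also expects some economic data to be missing and assumes they are missing at random.
- Section 10.2 gives the utility schedule: "The health utility questionnaire (EQ-5D) will be completed by the patient at 3, 6, 12, 18 and 24 months after randomization". The EORTC forms follow the same schedule, and both may be mailed.
- Appendix IX (Costs) says that total healthcare cost, covering all imaging and treatment, is "calculated for each patient and averaged across patients in each study arm".
- Appendix IX (Analysis) defines each cost and QALY term for the patients randomized to the arm. It takes the primary outcome of the trial as the measure of effectiveness.
- Appendix IX (Time Horizon): "Primary analysis will have a time horizon of two years reflective of the period of data capture within the clinical trial".
- Appendix IX (Costs), on what happens after recurrence: treatments received are captured, and the team will "obtain costs estimates for these but further data collection will not take place".

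**The concern.** Returning a questionnaire is an event after randomization, and it depends on survival and health. Using it as the entry condition removes patients who die before a first follow-up form, patients who never return one, and patients without a baseline form. Comparing the arms among those who remain is no longer the randomized comparison.

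The restriction is not needed for most of what the economic analysis uses. Sections 12.1 and 13.1 give every patient a treatment category, because planned treatment stands in when treatment is not completed. Deaths are followed for OS. Costs come from case-costing data, fee schedules and bottom-up costing, not from the EORTC forms. The condition also uses the wrong instrument: sections 5 and 10.2 treat the EORTC forms as the QoL questionnaires and EQ-5D as a separate utility questionnaire. A patient with complete EQ-5D data but no EORTC follow-up form would be left out of the QALY analysis.

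The economic analysis is part of a secondary objective (section 2.3), and section 15 says that the results will inform policy makers. Section 13.2 expects palliative treatment to rise from about 10% to 20% under PET-CT. If patients treated palliatively return fewer forms, the share excluded will differ between the arms.

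**Working it through.** **1. Which population each element uses**

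| Element | Population in the protocol |
|---|---|
| Primary outcome, EFS, OS | Full Analysis set (13.3) |
| All tests | intent-to-treat (13.1) |
| Cost and QALY terms in the ratios | patients randomized to each arm (Appendix IX, Analysis) |
| Effectiveness term | the primary outcome (Appendix IX, Analysis) |
| Economic outcomes as a whole | QoL Analysis set (13.3) |

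The last row does not fit the rows above it. The effectiveness term would be the primary outcome computed in a different set of patients, so the trial would carry two values of its own main result.

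**2. The plan's own figures**

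The protocol gives no figure for the economic analysis. The planned effect is (20% + 25%) − (10% + 15%) = 45% − 25% = 0.20. The planned size reproduces: a continuity-corrected two-proportion formula at 2:1 and 90% power gives 96 + 192 = 288, and exact Fisher power is 91.5%. This point does not affect either figure.

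**3. How many patients could be lost**

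The protocol gives no rate of form return. If 5, 10 or 15% in each arm lacked a baseline or any follow-up form (assumed), then 288 × 0.05, 0.10 or 0.15 ≈ 14, 29 or 43 patients would leave the economic analysis.

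**4. QALY difference**

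From section 13.2: palliative share 0.20 (PET-CT) and 0.10 (CT). Assumed: a fraction d of palliative patients dies before 3 months; two-year QALYs are 0.1 for them and 1.3 for everyone else; only those early deaths are excluded.

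- Excluded share: a = 0.20d (PET-CT), b = 0.10d (CT).
- Mean over all randomized patients: 1.3 − 1.2a and 1.3 − 1.2b. Mean in the QoL Analysis set: 1.3 in both arms.
- Shift in the difference caused by the restriction: 1.2(a − b) = 1.2 × 0.10d = 0.12d.
- d = 0.05, 0.15, 0.30 gives 0.006, 0.018, 0.036, in favour of PET-CT under these assumptions.

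The sign depends on which arm loses more patients. With assumed means of 1.4 for those included and 0.1 to 0.5 for those excluded, and no difference among those included, the QoL Analysis set always shows 0. The all-randomized difference is then:

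- 5% excluded in CT, 10% in PET-CT: −0.045 to −0.065
- 10% in CT, 5% in PET-CT: +0.045 to +0.065
- 5% in both: 0

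**5. Effectiveness term**

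Assumed: 90% of non-palliative patients return a form, and a fraction c of palliative patients does. In each arm

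E = (0.9 × EFRT + c × palliative) / (0.9 × standard + 0.9 × EFRT + c × palliative).

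- c = 0.7: PET-CT (0.225 + 0.140)/(0.495 + 0.225 + 0.140) = 0.365/0.860 = 0.4244; CT (0.135 + 0.070)/(0.675 + 0.135 + 0.070) = 0.205/0.880 = 0.2330; difference 0.191.
- c = 0.5: PET-CT 0.325/0.820 = 0.3963; CT 0.185/0.860 = 0.2151; difference 0.181.

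On all randomized patients the difference is 0.20.

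**The case against.** **The set is not as narrow as it may look.** A reader might infer that only full completers or two-year survivors are analysed. That is not so. Any one of five follow-up forms is enough, and forms may be mailed. A patient too ill at 3 months who returns a later form stays in, as does one who dies after returning the 3-month form. This limits how many are lost, but not the principle.

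**Some of the apparent conflicts can be reconciled.** The missing-at-random assumption in 13.1 can apply to gaps within the QoL Analysis set, since one form still leaves up to four missing. Averaging costs across patients in each arm names no analysis set. Appendix IX reports bootstrap intervals, so it can be argued that a sentence about tests does not reach the economic comparison. All three have some force. What remains is that the ratio terms are defined by randomization and that effectiveness is said to be the primary outcome, which 13.3 places on the Full Analysis set.

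**The bias is assumed and small.** Randomization balances underlying disease, and PET-CT changes who is labelled palliative. Tying early death to that label gives CT-arm patients with undetected metastases no early deaths. Patients enter with ECOG 0 to 2 and are being considered for curative treatment, so early death in 15 or 30% of palliative patients has no support in the document. The lowest QALY shift, 0.006, is about 2 days (0.006 × 365). The two illustrations also point in opposite directions: the QALY shift favours PET-CT, and the effectiveness shift goes against it. This stands, and no claim about net direction can be made.

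**Recurrence.** A reader might infer that costing stops at recurrence, or that costs and QALYs certainly cover different periods. Appendix IX supports neither. Treatments after recurrence are captured and costed, and the protocol does not say whether EQ-5D also stops then. What is unclear is whether any other resource use after recurrence is collected.

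**Conclusion.** The analysis-set point holds. Section 13.3 puts the economic analysis on a group selected after randomization, against the intent-to-treat rule in 13.1 and the definitions in Appendix IX. It does so for quantities that are largely known without a questionnaire.

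The size is illustrative only. The QALY difference shifts by 0.006 to 0.036 under the assumed early-death rates, and the effectiveness difference falls from 0.20 to 0.191 or 0.181 under the assumed return rates. Both rest on exclusion being concentrated in palliative patients and on the planned 10% and 20% shares. If equal shares with the same mean QALYs are excluded in the two arms, the QALY shift is zero. A reader might infer a known bias in favour of PET-CT, but the document does not support that.

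A narrower, secondary point also holds: the wording on data collection after recurrence does not sit well with a total healthcare cost over two years, and should be clarified.

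The primary outcome, EFS and OS are unaffected. This is a correction that should be made to a secondary objective and does not threaten the trial's main result.

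**What to change.** In section 13.3, replace the sentence on economic outcomes with wording to this effect:

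> Costs, QALYs and the effectiveness term of the cost-effectiveness ratio will be analysed on the Full Analysis set by randomized arm. Utility is zero from the date of death. Missing EQ-5D and cost data will be handled under the missing-at-random assumption of section 13.1, for example by multiple imputation. The QoL Analysis set is used for EORTC scores only.

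The exact imputation method can be left to the statistical analysis plan.

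In Appendix IX (Costs), state which resource use and which utilities are collected after recurrence up to month 24, so that the total cost and the QALYs cover the same two years.

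The cost is a change of wording, imputation code and modest extra analysis. If resource-use questions are to continue after recurrence, they can use contacts already scheduled to month 24. The price is reliance on missing at random for living patients with no follow-up form, whose utilities would be inferred from baseline data, treatment category and survival.

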### **13.4. Health Related Quality of Life Data**

Overall QoL will be assessed using the EORTC QLQ-C30 version 3, and disease-specific QoL using the EORTC QLQ-CX24. The mean and standard deviation of each QoL domain will be calculated at each time point, along with changes from baseline. The profile of the QoL scores will be plotted and compared between the two arms. A repeated measures regression model with an unstructured covariance structure will be used to evaluate the effect of the intervention longitudinally. Other covariance structures may be used if necessary. Descriptive statistics, plots and tables will also be used to explore for an effect on QoL between CT of the abdomen and pelvis + PET-CT and CT of the abdomen and pelvis alone over time. Effect of treatment regimen on QoL will also be investigated.

### **13.5. Health Economic Data**

A description of the economic analysis is described in *Appendix IX*.

### **13.6. Planned Interim Analysis**

One planned interim efficacy analysis will be performed after 50% of patients have been accrued. The Haybittle-Peto approach will be used, such that if the proportion of patients receiving standard pelvic chemo-radiation following CT abdomen and pelvis + PET-CT is significantly less (one-sided  $\alpha=0.001$ ) than the proportion of patients receiving standard pelvic chemo-radiation following CT abdomen and pelvis alone, then the Data Safety Monitoring Board (DSMB) will be expected to recommend to the Steering Committee that the trial should be discontinued early. In addition to the interim analysis based on efficacy, the DSMB will review accumulating safety data annually, starting approximately twelve months after study commencement. The Steering Committee will make the final decision about study continuation based on these recommendations.

### **14. CENTRAL ADJUDICATION**

A Central Adjudication Committee, composed of independent experts in oncology, will be available to review any disagreements about whether treatment was standard chemo-radiotherapy of curative intent, more extensive therapy of curative intent or non-curative therapy.

### **15. STUDY SIGNIFICANCE**

Cervical cancer is the second leading cause of cancer for women in their reproductive years. Currently, women with locally advanced cervical cancer receive chemo-RT. PET-CT has the potential to more accurately stage the cancer than CT or MRI by detecting tumour in para-aortic nodes and/or extra pelvic sites. In the former situation, RT will be altered by extending the fields to include the para-aortic nodes and the disease is potentially curable. In the latter situation the patient is counseled concerning the palliative nature of her disease and a long treatment course that is not curative is avoided. This study will address whether PET-CT adds a clinically meaningful difference in care. The economic analysis will evaluate the incremental cost associated with adding PET-CT to the current strategy of staging investigations. In addition, the results will inform policy makers on the value of adding PET-CT in this clinical situation.

### **16. ETHICAL AND REGULATORY STANDARDS**

This clinical trial will be conducted in accordance with the recommendations guiding physicians in biomedical research involving human patients adopted by the 18th World Medical Assembly, Helsinki, Finland 1964 and later revisions or the laws and regulations of the country, whichever provide the greater protection for the individual.

This clinical trial will be conducted in compliance with the ICH guidelines for Good Clinical Practice and will adhere to national laws and regulations of the country in which the study is performed.

Personnel involved in conducting this clinical trial will be qualified by education, training and experience to perform their respective tasks.

### **16.1. Informed Consent**

OCOG, as Sponsor, will provide each clinical centre with a sample Informed Consent Form. The Informed Consent Form used by the local Investigator for obtaining the patient's informed consent must be reviewed and approved by OCOG prior to submission to the appropriate Ethics Committee [Research Ethics Board (REB) or Institutional Review Board (IRB)] for approval/favourable opinion.

It is the responsibility of the local Investigator or a person designated by the local Investigator and under the Investigator's responsibility, to provide each potential study patient, prior to inclusion in the study, full and adequate verbal and written information regarding the objectives and procedures of the study and the possible risks involved. The patient must be informed about their right to withdraw from the study at any time. The patient must be allowed adequate time to make an informed decision.

Prior to a patient's participation in the study, the locally approved written Informed Consent Form must be signed, name filled in and personally dated by the patient or by the patient's legally acceptable representative, and by the person who conducted the informed consent discussion. A copy of the signed and dated written consent form document and any other written information should be provided to the patient.

### **16.2. Research Ethics Board (REB) or Institutional Review Board (IRB)**

Prior to the commencement of the study, the Investigator must submit this clinical trial protocol, the Informed Consent Form document, Investigator Brochure or product labeling information, recruitment materials/process, patient questionnaires, and any other written information to be provided to study patients to the appropriate Ethics Committee (REB/IRB) and is required to forward to OCOG a copy of the written and dated approval/favourable opinion signed by the Chairman with Ethics Committee (REB/IRB) composition.

The clinical trial (study number, clinical trial protocol title, version number and version date), the documents reviewed (clinical trial protocol, Informed Consent Form, Investigator's Brochure, etc.) and the date of review should be clearly stated on the written (REB/IRB) approval/favourable opinion.

During the clinical trial, any amendments or modification to the study protocol and/or Informed Consent Form document, as issued by OCOG, must be submitted to and approved by the local Ethics Committee (REB/IRB). The Ethics Committee (REB/IRB) should also be informed of any event likely to affect the safety of patients or the continued conduct of the study. Updates to the Investigator's Brochure should be sent to the Ethics Committee (REB/IRB).

Annual re-approval is required for as long as the study is open to patient accrual and/or patients are being followed and evaluated.

The Ethics Committee (REB/IRB) must be informed when the study is closed or has been suspended.

## **17. RESPONSIBILITIES OF THE INVESTIGATOR**

One Qualified Investigator (QI) will oversee the trial at each clinical centre. The QI undertakes to perform the study in accordance with this clinical trial protocol, ICH guidelines for Good Clinical Practice and the applicable national regulations and local REB/IRB requirements.

The QI may appoint other individuals as he/she deems appropriate to assist in the conduct of the study. All appointed designates will be listed and provided to OCOG (Sponsor). The appointed designates will be supervised by and under the responsibility of the QI.

For the purpose of ensuring compliance with the clinical trial protocol, ICH GCP and applicable regulatory requirements, the QI agrees to permit auditing by or on the behalf of OCOG and inspection by applicable regulatory authorities. The Investigator agrees to allow the auditors/inspectors to have direct access to his/her study records for review.

The QI must maintain confidential study documentation and ensure the retention of these study documents as per national regulations. The Investigator must notify OCOG (Sponsor) prior to destroying any essential documents following the completion or discontinuation of the clinical trial. If the QI can no longer ensure retention of the study documentation, the QI is required to inform OCOG (Sponsor) to arrange the transfer of the relevant records to a mutually agreed upon designee.

### **17.1. Source Document Requirements**

The OCOG Coordinating and Methods Centre will complete Case Report Form (CRF) verification by obtaining and reviewing local source documents, except for the pre-identified source data directly recorded in the CRF. The Informed Consent Form will include a statement by which the patient allows the Sponsor's authorized personnel, the Ethics Committee (REB/IRB), and the regulatory authorities to have direct access to source data which support the data on the CRFs. Such personnel, must maintain confidentiality according to privacy legislation.

